### Randomization, allocation concealment and blinding

2.7

Participants in the study will be randomized into treatment and control groups in a 1:1 ratio using a random assignment scheme generated by the “Proc Plan” procedure of SAS 9.4 statistical analysis software (SAS Institute, Cary, NC, United States). This scheme will be implemented through random allocation cards, which will be sealed in opaque envelopes by independent investigators, ensuring that the envelopes and card numbers match. The independent investigators responsible for randomization reviewed the envelopes and subsequently informed the acupuncturist of the patient’s group allocation. Patients are assigned to groups according to the allocation indicated on the card within the envelope they open, based on the order of their clinic visits. Each group, the EA group and the sham EA group, comprises 42 subjects. All participants will be informed that they have an equal chance of being assigned to either the EA or sham EA group. Interventions of two groups were administered by an acupuncturist who had specific training in the field, with a minimum of 5 years of experience. Participants, information assessors, and statisticians will not be able to predict group assignments throughout the study, except for the acupuncturist. To ensure the success of the blinding, communication regarding the treatments is minimized, appointments are scheduled, and patients are treated in separate consultation rooms while lying supine and wearing eye masks. Moreover, all researchers who have received training on the implementation of this research will strictly abide by the principle of departmental separation.

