### Study design

2.1

This study is a randomized, single-blinded, sham-controlled trial that has been registered with the Chinese Clinical Trial Registry (ChiCTR2400083326. The protocol adheres to the Standard Protocol Items: Recommendations for Intervention Trials (SPIRIT) 2013 (34), as detailed in supplementary file 1. Patients or the public were not involved in the design, conduct, reporting, or dissemination plans of our research. Approval for this study was approved by the Medical Ethics Committee of LongHua Hospital Shanghai University of Traditional Chinese Medicine (NO.2024LCSY020). Any modifications to the protocol will be reported to both the ChiCTR and the Medical Ethics Committee. This protocol is version 1.0. The flowchart of the study is shown in **Figure 1** (Flowchart of the study), while the schedule of enrollment, interventions, and assessment is shown in **Table 1** (Schedule of enrolment, interventions, and assessment).

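### Section 2.7 contradicts itself on who opens the allocation envelope; on its plain reading patients open it and see their group, which is incompatible with the stated participant blinding

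*Protocol article*

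**What the plan says.** All the statements on envelope handling are in section 2.7 of the protocol article.

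- Preparation: "This scheme will be implemented through random allocation cards, which will be sealed in opaque envelopes by independent investigators". The envelope and card numbers are to match.
- Handling, first statement: "The independent investigators responsible for randomization reviewed the envelopes and subsequently informed the acupuncturist of the patient’s group allocation".
- Handling, second statement, which follows directly: "Patients are assigned to groups according to the allocation indicated on the card within the envelope they open". The sequence is that in which the patients attend the clinic.
- Blinding: "Participants, information assessors, and statisticians will not be able to predict group assignments throughout the study, except for the acupuncturist".
- Information given to patients: "All participants will be informed that they have an equal chance of being assigned to either the EA or sham EA group".

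Section 2.1 labels the design: "This study is a randomized, single-blinded, sham-controlled trial". Section 2.10 asks each participant, after the last treatment, to choose between EA, sham EA and uncertain. Section 2.13 analyses those answers with Bang's Index. Section 2.15 says recruitment is under way.

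**The concern.** The two handling sentences give the envelope to different people. If patients open it, they learn whether they are to receive EA or sham EA, and the participant blinding claimed in the same section is lost before the first session.

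Participant blinding carries much of this design. The acupuncturist knows the allocation, and the Discussion accepts that double blinding is not feasible. The trial therefore invests in keeping the patient unaware: a blunt needle that does not penetrate, a power cord with hidden cut wires, eye masks, separate rooms and a device meant to look the same in both arms. None of this helps a patient who has read the card.

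The primary outcome, PSQI change at week 8, is a questionnaire about the patient's own sleep. The ISI and the sleep diary also rest on the patient's own account. A patient who knows the allocation may report more improvement on EA, or less on sham, whatever the physiological effect. That would enter the primary comparison directly and could not be removed at analysis.

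**Working it through.** No arithmetic decides this point. The check is whether the statements can all be followed at once.

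**1. Who is meant by *they* in the second handling sentence?** The grammatical subject is the patients. The same sentence orders the allocation by *their* clinic visits, which can only be the patients' visits. The natural referent of *they* is therefore the patients.

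**2. What does the card show?** The sentence says it indicates the allocation. Nothing in the article says that the card carries only a code, or that it is withheld once the envelope is open. A patient who opens it would learn the group.

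**3. Can this stand with the preceding sentence?** There, the independent investigators learn the allocation from the envelopes and pass it to the acupuncturist. If they do this, the patient has no need to open anything. If the patient opens a sealed envelope, it is unclear how the investigators reviewed it. The two sentences do not describe one procedure.

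**4. Can it stand with the blinding statements?**

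| Statement | If an investigator opens the envelope | If the patient opens the envelope |
|---|---|---|
| Section 2.7: participants unaware throughout, acupuncturist the only exception | Consistent | Contradicted |
| Section 2.1: single-blinded, sham-controlled | Consistent | Contradicted as regards patients |
| Section 2.10: guess of group after the last session | Informative | Only records what the patient has read |
| Section 2.13: Bang's Index | Interpretable | Not interpretable as a test of the sham |
| Section 2.7: patients told of an equal chance | Consistent | Also consistent, so it does not discriminate |

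**5. Which outcomes are exposed?** The Introduction calls the ISI a self-assessment tool. Sections 2.8 and 2.9.2 have participants keep the diary and record subjective estimates. The article does not literally call the PSQI self-reported. That it is completed by patients follows from its content and from section 2.4, which requires patients to be able to understand and complete the scales. Actigraphy is described as objective and is less exposed. Section 2.9.2 does not say who records medication use, so it is left out here.

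**6. Size.** The planned difference in section 2.12 is 6.24 − 3.69 = 2.55 PSQI points. The documents give nothing on how much of either arm's change depends on belief about allocation, so the bias cannot be expressed as a share of it.

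**The case against.** The strongest reply is that the literal reading hangs on one pronoun, while the rest of the article points the other way. Having investigators inform the acupuncturist has little purpose if patients open their own cards. The sham device, the eye masks and the guess test all presuppose unaware patients. The section mixes tenses, so loose drafting is plausible, and *they* may mean the investigators of the preceding sentence.

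This stands as a limit on what can be concluded about conduct. It does not remove the contradiction: the text as printed names the patient, and no sentence corrects it. Nor is this detail that an article leaves to a fuller protocol, because the article states the step and states it inconsistently.

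Three stronger readings are tempting but unsupported.

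- *Patients have in fact been unblinded.* The article does not show what staff do.
- *Allocation may be seen before the patient is committed to the trial.* Neither handling sentence gives a time relative to enrolment, and section 2.2 puts eligibility assessment and written consent before randomisation.
- *The bias can be sized from the pilot sham change of 3.69 points.* Assuming a quarter to a half of it would give 0.25 × 3.69 = 0.92 to 0.5 × 3.69 = 1.85 points, but those fractions have no source in the documents. The 3.69 is also a before-after change. In this trial such a change would include sleep hygiene advice, permitted changes in hypnotic dose, and probably regression to the mean after entry at PSQI above 10. It is not an upper bound either, since expectation could also raise the response to EA.

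**Conclusion.** The point holds as an internal contradiction with a serious conditional consequence. Section 2.7 gives two incompatible accounts of who opens the envelope. The second, on its plain reading, would disclose allocation to patients and so contradict sections 2.1, 2.7 and 2.10. If followed, it would defeat the purpose of the sham control for the primary outcome and leave the ISI and diary results open to the same bias.

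The size of that bias cannot be computed from the documents, and no figure is offered. The conclusion rests on two readings of the text: that *they* refers to patients, and that the card shows the group in clear. If *they* means the investigators, the defect is one of wording and participant blinding is not impaired by this step. Confidence in the literal reading as a description of conduct is moderate at most. The text needs correcting on either reading, because staff are recruiting now and could act on either sentence.

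**What to change.** Replace the two handling sentences with one procedure. After written consent and baseline assessment, the independent randomisation investigator opens the next numbered envelope and tells only the acupuncturist. State explicitly that patients, assessors and statisticians never see the card.

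Then establish which procedure has been used for patients already randomised. If no patient opened an envelope, a clarification of the text is enough. If any did, report how many and in which arm, and do not claim participant blinding for them; correcting the sentence does not repair their data.

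The cost is a short text change, a note to site staff and a check of how envelopes have been handled so far. The independent investigators are already part of the plan, so no extra staff are needed. The sample size and the analysis are unaffected.

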### Interventions

2.8

All participants will receive three sessions per week (every other day), each lasting for 30 minutes, resulting in a total of 24 sessions over the 8-week course. Follow-up assessments will occur at weeks 12 and 20. Participants were asked to return for follow-up visits at weeks 12 and 20.

Participants in both groups will receive sleep hygiene guidelines (e.g., avoiding coffee, tea, alcohol, etc.; maintaining a routine; creating an appropriate sleep environment; and attending to emotional self-regulation) through conversation. These instructions will serve as the primary treatment for GAD-related insomnia. The conversations will be conducted from week 0 to week 8. Additionally, participants will be instructed to maintain a sleep diary for 9 weeks, covering week 0 to 8.

During the trial, both the type and dosage of anti-anxiety medications will remain unchanged. The type of sedative-hypnotic medications will also remain consistent, however, dosage adjustments may be made based on the patient’s condition, with detailed records maintained. In cases of severe insomnia, the temporary use of Zolpidem or Eszopiclone is permitted for no more than three consecutive days with thorough documentation of such instances.

#### Treatment group

2.8.1

Participants in the treatment group will receive acupuncture at Baihui(GV20), Shenting (GV24), Yintang (GV24^+^), Neiguan (PC6), Shenmen (HT7), Zusanli (ST36), Sanyinjiao (SP6), and Taichong (LR3). Among these acupoints, GV20, GV24, and GV24^+^ are located on the anterior midline, while the others are applied bilaterally (**Figure 2** Locations of acupoints). Acupoint Location: refer to *The Location of Acupoints: State Standard of the People’s Republic of China* [GB/T 12346–2021]). The acupuncture technique for each point is described in **Table 2** (Locations and manipulations of acupoints in the treatment group). For the treatment group, patches will be attached to the acupoint (**Figure 3** EA and sham EA manipulation). Needles will be inserted through the patches into the skin, and all needles will undergo acupuncture manipulation such as lifting, twirling, and thrusting to achieve “*De qi*”, which is characterized by sensations of swelling, soreness, numbness, and heaviness. GV20 and GV24^+^ will be connected to EA with a continuous wave of 2 Hz (40) and an intensity adjusted to the patient’s comfort level, lasting for 30 minutes. In this study, sterile acupuncture needles (size 0.25*25mm and 0.25*40mm from Suzhou Medical Supplies Factory Co.’s Hwato) and an electrical stimulator (SDZ-V EA instrument, Hwato, Suzhou, China) will be utilized.

**Figure 2 f2:**
[figure not shown]
Locations of acupoints. Image of acupoints for treatment and control group.

**Table 2 T2:** Locations and manipulations of acupoints in the treatment group.

Acupoint	Location	Manipulation
Baihui (GV20)	On the head, 5 *cun* superior to the anterior hairline, on the anterior median line.	Insert the needle transversely for 0.5-0.8 *cun*, and connect to EA with a continuous wave of 2Hz.
Shenting (GV24)	On the head, 0.5 *cun* superior to the anterior hairline, on the anterior median line.	Insert the needle transversely for 0.5-0.8 *cun*.
Yintang (GV24^+^)	On the forehead, at the midpoint between the medial ends of the eyebrows.	Insert the needle transversely for 0.3-0.5 *cun*, and connect to EA with a continuous wave of 2Hz.
Neiguan (PC6)	On the anterior aspect of the forearm, 2 *cun* superior to the palmar wrist crease, between the palmaris longus tendon and the flexor carpi radialis tendon.	Insert the needle perpendicularly for 0.5-1.0 *cun*.
Shenmen (HT7)	On the anterior aspect of the wrist, at the ulnar end of the palmar wrist crease, radial to the flexor carpi ulnaris tendon.	Insert the needle perpendicularly for 0.3-0.5 *cun.*
Zusanli (ST36)	On the lateral aspect of the leg, 3 *cun* distal to the lower border of the patella and 1 finger-breadth lateral to the anterior crest of the tibia.	Insert the needle perpendicularly for 1.0-1.5 *cun.*
Sanyinjiao (SP6)	On the medial aspect of the leg, 3 *cun* superior to the rominence of the medial malleolus, posterior to the medial border of the tibia.	Insert the needle perpendicularly for 1.0-1.5 *cun.*
Taichong (LR3)	On the dorsum of the foot, between the first and second metatarsal bones, in the depression anterior to the junction of the bases of the two bones, or over the dorsalis pedis artery.	Insert the needle perpendicularly for 0.5-1.0 *cun.*

**Figure 3 f3:**
[figure not shown]
EA and sham EA manipulation. Electroacupuncture and sham Electroacupuncture manipulation.

#### Control group

2.8.2

The acupoints selected for patients in the control group are identical to those used in the treatment group. Patches are affixed to the acupoints (**Figure 3** EA and sham EA manipulation), allowing sham needles to be inserted through the patch and reach the surface of the skin. Because of the flat needle tip, it cannot penetrate the skin (41, 42) (Patent Number: ZL 2023 2 0605629.3). GV20 and GV24^+^ are connected to the same type of electrical stimulator via a special power cord, the internal wires of which have been cut and are not visible externally, lasting for 30 minutes. As a result, the EA device appears to be connected, but no current flows through the wires. In this group, the sham needles (size 0.25*25mm from Guizhou Andi Medical Equipment Co.) and the same electrical stimulator will be utilized.

### Outcome

2.9

#### Primary outcome

2.9.1

The primary outcome measure is the change in the Pittsburgh Sleep Quality Index (PSQI) score at week 8, compared to baseline.

PSQI is used to assess the sleep quality of subjects over the past month. It is applicable for the evaluation of sleep quality in patients with sleep disorders. The PSQI consists of 19 questions divided into 7 dimensions, including sleep quality, sleep efficiency, nocturnal activities, early waking, sleep medication, sleep satisfaction, and daytime fatigue. Due to its simplicity, high reliability, and validity, and its high correlation with polysomnographic results, it has become a commonly used scale in research and psychiatric clinical assessments (22).

#### Secondary outcome

2.9.2

The secondary outcomes include the following seven items:

The change in HAMA score compared to the baseline. The Hamilton Anxiety Rating Scale (HAMA), one of the first rating scales to measure the severity of perceived anxiety symptoms, is still in use today and is considered one of the most widely used rating scales. It can effectively compare changes in symptoms before and after treatment to assess the effectiveness of the treatment (26). It will be assessed at weeks 4, 8, 12, and 20.The change in PSQI score compared to the baseline will be evaluated at weeks 4, 12, and 20.The change in Insomnia Severity Index (ISI) score relative to the baseline. It will be evaluated at weeks 4, 8, 12, and 20.Sleep diary entries: Records subjective estimates daily from week 0 to week 8. The recording includes Sleep Onset Latency, Wake After Sleep Onset, Early Morning Awakening, Total Sleep Time, and Sleep Efficiency.The change in the 12-item Short-Form Health Survey (SF-12) score compared to the baseline, which will be evaluated at weeks 8 and 20.Actigraphy sleep assessment: Patients will wear an actigraphy motion recorder for four days during weeks 0 and 8. The recordings will include total sleep time, sleep awakening numbers, wake after sleep onset, average duration of awakening, and sleep efficiency. This device will objectively assess the subjects’ sleep quality.Weekly usage of medication: The usage of sedative-hypnotic medication will be recorded for each group of subjects weekly from week 0 to 20. Adjustments to sedative-hypnotic medication during the treatment and follow-up period will be documented strictly, including the name, dosage, and frequency of the medication.

### Blinding assessment

2.10

After participants complete their final treatment, an independent assessor will present them with three options: EA, sham EA, and uncertainty. Their selections will be documented, and the results will be used to assess the success of the blinding process.

### Safety evaluation

2.11

Treatment-related adverse events (AEs) include dizziness, fainting, hematoma, needle breakage, infection, and exacerbation of the condition due to excessive stimulation from acupuncture or EA. Each AE will be documented with details regarding the date of occurrence, severity, relevance, and resolution. Prior to the trial, researchers will undergo a rigorous training program to ensure that they are proficient in both the treatments and the management of AEs. In the event of any observed AEs, the acupuncturist will promptly assess the severity and take appropriate actions. These may include immediate needle removal and cessation of treatment, providing rest, applying gentle pressure to mitigate bleeding and hematoma formation, or referring the patient to a surgeon or other medical professional in cases of needle breakage or infection. Serious AEs will be reported to the safety committee without delay and managed actively. The anxiety level of the participants was evaluated by a trained assessor, who will terminate the trial based on the outcome. Finally, researchers will analyze patient case report form (CRF) data on AEs to evaluate the occurrence of adverse events in this trial, thereby providing valuable insights for the design of future trials.

### Sample size calculation

2.12

The PASS software (version 15.0.5, NCSS, LLC) was used to calculate sample size with α of 0.05 (two-tailed), power of 80%, and ratio of 1:1. Based on our pilot study, the change in PSQI score of patients with GAD-related insomnia between week 8 and baseline was calculated. For the treatment and control groups, the mean ± standard deviation (SD) was 6.24 ± 3.63 and 3.69 ± 2.45, respectively. The calculated sample size for each group is 33 cases; considering a 20% dropout rate, each group needs 42 participants, totaling 84 participants for both groups.

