### Statistical methods

2.13

Statistical analysis, including a full analysis set based on the intent-to-treat principle and a per-protocol set, will be conducted with SPSS 26.0 software. Continuous variables such as the change in PSQI, HAMA, ISI, SF-12 score compared to the baseline and indicators of sleep diary entries and actigraphy sleep assessment, which is described as mean ± SD or median (interquartile range) will be analyzed by t-test or rank-sum test while categorical variables such as the proportion of patients with reduced medication represented by frequency (composition ratio) will be analyzed by chi-square or Fisher’s exact tests. CIs will be set at 95% with a significance level of 5% (P < 0.05). The success of blinding will be evaluated through Bang’s Index by using the “χ² test” procedure of SPSS 26.0 software. In addition, A subgroup analysis will be conducted based on factors such as age, gender, type of anti-anxiety medication, and type of sedative-hypnotic medication by the “Split File” procedure of SPSS 26.0 software. The confidence interval will be set at 95%, with a significance level of 5% (P < 0.05).

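### The stated 33 per group does not follow from the stated inputs: at 80% power they give 25 per group, and 33 per group gives about 91%

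*Protocol article*

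**What the plan says.** Section 2.12 (Sample size calculation) of the protocol article reports a calculation in PASS "with α of 0.05 (two-tailed), power of 80%, and ratio of 1:1". The endpoint is the PSQI change from baseline to week 8. For the treatment and control groups in the pilot study, "the mean ± standard deviation (SD) was 6.24 ± 3.63 and 3.69 ± 2.45, respectively". The result follows directly: "The calculated sample size for each group is 33 cases; considering a 20% dropout rate, each group needs 42 participants", which makes 84 in total.

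The section names neither the test nor the variance option used in PASS, and it does not say that a single SD was applied to both groups. Section 2.13 (Statistical methods) says that continuous outcomes, including the PSQI change, "will be analyzed by t-test or rank-sum test".

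**The concern.** Every input needed to recompute the sample size is printed next to the result, and the result does not come out. The gap is 8 patients per group (33 against 25), too large for rounding or a software convention.

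This calculation is the only justification given for the target of 84, and its power figure is likely to be repeated in the trial report. As written, a reader takes 33 evaluable patients per arm as the minimum for 80% power. Either the trial has clearly more power than it claims, or it was planned on an assumption that the text does not disclose. The difference matters if dropout exceeds 20% or the result is null. With the stated SDs there is a wide margin below 33 per arm; with SD 3.63 in both arms there is none.

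**Working it through.** **Inputs (all from section 2.12).** Difference 6.24 − 3.69 = 2.55; SDs 3.63 and 2.45; two-sided alpha 0.05; power 80%; 1:1 allocation; 20% dropout.

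**Step 1. Normal approximation.**
n per group = (z₀.₉₇₅ + z₀.₈₀)² × (SD₁² + SD₂²) / difference²
= (1.960 + 0.842)² × (13.177 + 6.003) / 6.503
= 7.849 × 2.950 = 23.15, so 24 per group.

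**Step 2. t-test power (noncentral t), each SD in its own arm.** The root-mean-square SD is √(19.179/2) = 3.097, a standardised effect of 2.55/3.097 = 0.823.

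| n per group | Welch | Equal-variance t |
|---|---|---|
| 24 | 79.5% | 79.7% |
| 25 | 81.2% | 81.4% |
| 32 | 89.9% | 90.0% |
| 33 | 90.8% | 90.9% |
| 42 | 96.1% | 96.2% |

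Both versions need 25 per group for 80% power. At 33 the power is about 91%.

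**Step 3. Rank-sum test, the alternative in section 2.13.** With normal data and 5,000 simulated trials, power is 79.7% at 26, 81.5% at 27 and about 89% at 33 per group. So 26 to 27 per group are needed, which does not explain 33 either.

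**Step 4. What returns 33.** Changing one stated input gives 33 in two ways:

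- SD 3.63 in both arms, t-test, 80% power. The normal approximation is 7.849 × 2 × 13.177 / 6.503 = 31.8, so 32. The t-test gives 79.0% at 32 and 80.2% at 33, so 33 is the smallest adequate n.
- Both stated SDs, Welch test, 90% power: 89.9% at 32 and 90.8% at 33, so again 33.

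Other combinations also return 33, for example two-sided alpha 0.025 with 85% power and the root-mean-square SD. They change more than one stated input.

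**Step 5. Dropout.** 33/0.8 = 41.25, rounded up to 42: the article's step is correct. From 25 the same step gives 25/0.8 = 31.25, so 32 per group and 64 in total. The planned 84 is 84/64 = 1.31 times that.

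**Step 6. What the two readings imply.**

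- Stated SDs: 33 per group detects a difference of about 2.18 points at 80% power (Welch), not 2.55. Losses could reach 17 of 42 per arm (about 40%), leaving 25, before power fell close to 80%.
- SD 3.63 in both arms: 33 per group is the minimum, and 25 per group would give only 68%.

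**The case against.** The strongest reply is that section 2.12 presents the two SDs as pilot results and does not say that both were entered in PASS. If 3.63 was entered as a deliberately cautious common SD, then the alpha, the 80% power, both pilot SDs and the 33 are each literally true, and only a clause is missing. A condensed article may leave the choice of PASS procedure to the full protocol. The discrepancy is also harmless for power: on either of the two simple readings, 33 evaluable patients per arm reach at least 80% for 2.55 points.

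Much of this stands. The common-SD reading is coherent and may well be what happened, and the trial is not underpowered on either reading. It does not remove the mismatch. The article sets out an SD for each arm and then a result presented as calculated from them, without mentioning that one SD was set aside. A reader who uses the printed figures gets 25. The document also gives no basis for choosing between the common-SD and the 90%-power explanations.

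**Conclusion.** The concern holds. On the stated inputs, 80% power needs 25 per group (24 by normal approximation, 26 to 27 for a rank-sum test), and 33 per group gives about 91%. Either the power or the SDs actually used differ from what a reader would take from section 2.12, or the 33 itself is wrong. The planned 84 is about 31% more than the 64 that the stated inputs require.

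The t-test figures assume approximately normal changes, with the pilot means and SDs taken at face value. The fault lies in the reported calculation: it does not threaten the trial's power, and the dropout inflation is right.

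**What to change.** Keep 84 patients. Check the PASS output and correct the sentence in section 2.12 to match it, in one of two forms:

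- 33 evaluable patients per group give about 91% power for a 2.55-point difference with SDs 3.63 and 2.45; or
- the calculation used a common SD of 3.63 in both groups, a conservative choice, with 80% power.

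Name the test and variance option used. It would also help to give the difference that 33 per group detects at 80% power: about 2.18 points with the stated SDs, or about 2.55 with a common SD of 3.63.

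The cost is one corrected sentence, repeated wherever the calculation is reported. Enrolment, conduct and analysis do not change.
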